### Randomization Process

Stratified constrained randomization was used to ensure both spatial and covariate balance across groups. As study strata, 3 study provinces (Cajamarca, Cajabamba, and San Marcos) were used. Within each stratum, communities were allocated with ratios 3.6:1:3.6 for the control group, home visit group, and the Afini group, resulting in a final sample of 72 clusters in both the control group and Afini group and 20 clusters in the home visit group. A total of 1000 potential cluster allocations were randomly drawn using the Stata SE (version 16.0; Stata Corp) software package. We then chose the allocation minimizing mean differences across the 3 arms concerning variables such as cluster population size, cluster number of births, cluster altitude, household cell phone ownership, education of caregiver, and household wealth. Information on these covariates was obtained from governmental sources and validated by our field staff.

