### Primary and Secondary Outcome Measures

The primary study outcome will be children’s overall development at the age of 2.5 years. Children’s development will be assessed using the long form of the Global Scales for Early Development (GSED) [38]. The GSED is a new global open access tool designed to provide a standardized method for measuring the development of children up to 36 months of age in low-resource settings. We will use the long form of the GSED tool, which allows for a direct assessment of children’s development through trained assessors.

Secondary outcomes include (1) caregiver-reported early child development in motor, cognitive, language, and socio-emotional domains; (2) quality of a caregiver-child relationship; (3) screen time with and without a child being present; (4) primary female caregiver’s parenting behaviors; (5) parenting attitudes; and (6) mental health. Table 1 summarizes the measures to be collected at baseline and endline—all measures will be applied to the full sample, that is, to all participants independent of their random group assignment. Given that children were very young at baseline (6 months on average), detailed assessments of child development and caregiver-child interactions seemed unlikely to yield much insight at baseline. For overall child development, we used a caregiver report (Caregiver Reported Early Development Instruments [39]) at baseline and will use a more detailed direct observation tool (GSED) at endline. Sociodemographic factors collected at baseline will be used as controls in the final analysis.

**Table 1 table1:** Overview of constructs and measures used at baseline and endline.

Construct and measures		Time of assessment

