### Statistical Analysis

After confirming the psychometric reliability and validity of our key variables, we will perform a descriptive analysis (means and percentages) for the main characteristics and calculate prevalence and proportions for the primary outcomes. We will use standard linear regression models to assess the impact of the 2 intervention arms on child development. The primary outcome variable will be overall development as measured by the GSED, normalized to a developmental *z* score with a mean (0, SD 1) in the global reference population. Our primary empirical approach will be intent-to-treat, that is, comparing average outcomes across the 3 arms (independent of intervention compliance) with average outcomes in the control group. We will also conduct additional per-protocol analyses measuring mean differences between compliant children in the intervention arms with compliant children in the control group. For the home visit group, compliance will be defined as receiving at least 18 out of the 36 anticipated visits over the 18-month intervention period. Compliance with the Afini intervention will be defined as having interacted with the system at least once per month for at least 6 months in the observation period. Cluster-robust standard errors will be used to account for the cluster-level randomization of the intervention. Separate models will be estimated with and without baseline covariates.

Specifically, we will assess and control for household factors, caregiver factors, and child factors. Structural equation modeling will be used to test subgroup and mediation effects.

We will calculate the intervention’s cost-effectiveness by comparing the developmental outcomes observed in the 2 intervention arms to the average developmental levels in the control arm to the costs of the 2 interventions per child.

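### Two models of the primary outcome are planned and neither is named primary; the text ties neither to the province strata or the cluster variables that constrained the randomisation

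*Protocol article*

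**What the plan says.** Statistical Analysis sets the model form ("We will use standard linear regression models to assess the impact of the 2 intervention arms on child development") and the variance estimator ("Cluster-robust standard errors will be used to account for the cluster-level randomization of the intervention"). On covariates it says "Separate models will be estimated with and without baseline covariates", followed by "Specifically, we will assess and control for household factors, caregiver factors, and child factors". Intention-to-treat is named as the primary approach. That settles who is compared, not which of the two models decides.

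Primary and Secondary Outcome Measures speaks of a single adjusted analysis: "Sociodemographic factors collected at baseline will be used as controls in the final analysis".

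Randomization Process describes the design that the model should reflect: "Stratified constrained randomization was used to ensure both spatial and covariate balance across groups", with "As study strata, 3 study provinces (Cajamarca, Cajabamba, and San Marcos) were used". Of 1000 candidate allocations one was kept: "We then chose the allocation minimizing mean differences across the 3 arms concerning variables such as cluster population size". The list continues with births, altitude, cell phone ownership, caregiver education and wealth.

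**The concern.** Two statements answer the same question differently: one promises controls in the final analysis, the other promises two models and ranks neither. A reader cannot tell which estimate and p-value decide the trial, and the choice could be made after both are known.

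The version without covariates also leaves out, by construction, the variables on which the allocation was stratified and balanced. An analysis that ignores such variables reports a standard error suited to unconstrained allocation. If they predict development, that standard error is too large and precision is lost. Finally, Table 4 shows Afini somewhat above control on several baseline measures related to the outcome, so the two versions could give different estimates.

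**Working it through.** **Inputs.** From Sample Size Calculations: 15 (SD 5) children per cluster, ICC 0.12, alpha 0.05 (two-sided assumed), attrition 15%, effects 0.25 SD (Afini) and 0.5 SD (home visit), each against control. From Randomization Process: 72/20/72 clusters, three strata, best of 1000 draws. From Table 4: baseline means and SEs. The prognostic strength of the design variables and the balance metric are not given, so both are assumed.

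**1. The plan's own figures.** 164 × 15 = 2460, the recruitment target; 3.6 × 20 = 72. The article states no power. With 15 × 0.85 = 12.75 children per cluster, the variance of a cluster mean is 0.12 + 0.88/12.75 = 0.1890. The SE for Afini v control is √(2 × 0.1890/72) = 0.0725, and power at 0.25 SD is Φ(0.25/0.0725 − 1.96) = Φ(1.49) ≈ 93%. Across cluster-size variation and with or without attrition it runs from 91.5% to 94.4%.

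**2. Standard error of the unadjusted model.** If the design variables explain a share R² of the between-cluster variance and are perfectly balanced, the true SE is √(2 × [0.12(1 − R²) + 0.0690]/72). This gives 0.0626 at R² = 0.40 and 0.0540 at 0.70, while the unadjusted model still reports about 0.0725. Real balance is imperfect, so best-of-1000 allocation on six covariates was simulated (3000 trials per setting for the 25% and 50% rows, 1500 for the others):

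| Assumed share explained | True SE, unadjusted | Mean reported SE | Excess width | Type I error, unadjusted | Type I error, fully adjusted |
|---|---|---|---|---|---|
| 0% | 0.0739 | 0.0723 | none | 5.2% | 5.7% |
| 25% balancing variables | 0.069 | 0.0744 | 7–8% | 3.7% | not shown |
| 50% balancing variables | 0.067 | 0.0745 | 11% | 3.1% | not shown |
| 30% balancing variables + 10% province | 0.0653 | 0.0726 | 11% | 3.0% | 5.3% |
| 50% balancing variables + 20% province | 0.0576 | 0.0725 | 26% | 1.2% | 4.5% |

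Province terms alone do not restore the level: 3.6% and 1.8% in the last two rows.

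**3. Power.** For Afini v control at 0.25 SD (30% + 10% setting), power is 94.8% unadjusted and 97.1% adjusted. For Afini v home visit, the planning effects imply 0.5 − 0.25 = 0.25 SD. With SE = √(V × [1/72 + 1/20]):
- unadjusted, V = 0.1890: SE 0.110, power 62%;
- R² = 0.25, V = 0.1590: SE 0.101, power 70%;
- R² = 0.50, V = 0.1290: SE 0.091, power 79%.

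Simulation gave 62% rising to 70–78%, or 63–73% with a small-sample SE.

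**4. Baseline differences, Afini minus control (Table 4).** z = difference/√(SE₁² + SE₂²). Each mean is rounded to one decimal, so each difference is uncertain by ±0.1.

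| Measure | Difference | SE | z | z range from rounding |
|---|---|---|---|---|
| CREDI | 0.2 | 0.093 | 2.16 | 1.1–3.2 |
| Father's education | 0.2 | 0.099 | 2.02 | 1.0–3.0 |
| Mother's education | 0.2 | 0.113 | 1.77 | 0.9–2.7 |
| SES index | 0.3 | 0.170 | 1.77 | 1.2–2.4 |
| Stimulation index | 0.1 | 0.085 | 1.18 | 0.0–2.4 |

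The standardised differences are about 0.05 to 0.21 SD (covariate ICC assumed 0 to 0.3). A difference of 0.1 to 0.2 SD with an assumed slope on GSED of 0.1 to 0.4 would shift the unadjusted Afini estimate by 0.1 × 0.1 = 0.01 to 0.2 × 0.4 = 0.08 SD.

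**5. Leaving the choice open.** Under the null, the chance that at least one model is significant lies between the larger of the two rates and their sum: 5.3% to 8.3% in the 30% + 10% setting, 4.5% to 5.7% in the 50% + 20% setting. These are bounds only. The two estimates are strongly correlated, so the upper ends are unlikely.

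**The case against.** Only a journal article is shown. A full covariate list, stratum terms included, may sit in an analysis plan, and its absence here is no error. Nothing in the article excludes these terms. The wording leans towards adjustment, and education, wealth and phone ownership fit under household and caregiver factors. Baseline CREDI could be a child factor. All of this stands. What it does not settle is which of two announced models is primary, because that is stated in two ways that do not agree.

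A reader might infer that the unadjusted model gives misleadingly significant results. The documents do not support that. Any error in its SE is towards width, and it depends on a prognostic strength that is nowhere given; with none, the type I error is 5.2%.

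A reader might also infer from Table 4 that the Afini estimate will be biased upwards. That is not supported either. The differences are small, probably correlated with one another, picked from 13 rows and sensitive to rounding. CREDI is not shown as age-standardised, and the Afini children are listed as 5.1 v 5.0 months old. The adjusted model, also planned, could deal with them.

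The two arguments also pull against each other: so far as balance was lost between allocation and enrolment, the excess width shrinks. Table 4 counts 67/19/78 clusters against 72/20/72 as randomised (both total 164). This needs reconciling, because the constrained balance belongs to the randomised allocation.

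Lastly, the larger power gain concerns Afini v home visit, which Study Design names as an aim but Sample Size Calculations does not power. It is a secondary argument.

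**Conclusion.** The point holds as one about an unresolved choice of primary model, with a design-based reason for resolving it towards adjustment. If the design variables explain 25% to 70% of between-cluster variance (assumed), the unadjusted SE is about 7% to 26% too wide and its type I error about 1% to 4%. This costs precision and does not threaten validity; at zero prognostic strength there is no cost. For Afini v control the gain is about 2 percentage points of power. For Afini v home visit it may be 8 to 16 points before any small-sample correction (62% to 70–78%). The baseline differences are a further reason to prefer adjustment and do not demonstrate bias. The change is worth making because it is nearly free and removes a choice that could otherwise follow the results.

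**What to change.** Name one primary intention-to-treat model: GSED z score on the two arm indicators, province fixed effects, the variables actually used to constrain the randomisation, and age-adjusted baseline CREDI. State the constraint variables in full, because the article introduces its list as examples. Report the model without covariates as a sensitivity analysis, and align the wording of the outcomes and analysis sections. Further covariates are optional.

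The cost is wording only: the allocation variables are already held and CREDI was collected at baseline. The model spends a few degrees of freedom. With about 20 home-visit clusters this calls for a small-sample correction to the cluster-robust SE, which takes back part of the gain in the Afini v home visit comparison (63–73% instead of 70–78% in the simulation).

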### Ethical Considerations

The study was approved by the University Peruana Cayetano Heredia institutional review board in Lima, Peru (SIDISI: 202522-Ref 030-03-21) and the Ethics Commission for Northwest and Central Switzerland (EKNZ: AO_2021-00002). All participants signed an informed consent before participating in any project-related activity. Verbal consent was asked for key informant interviews and focus group discussions during the pilot phase. The nature of the study was thoroughly explained to all participants, and all questions were answered before obtaining informed consent. Community leaders and local authorities are aware of the study.

## Results

As shown in Table 2, enrollment and baseline data collection were completed in March 2023, and endline assessments were launched in September 2023. Table 4 shows descriptive statistics for the baseline sample by study arm. On average, children were 5 months old at baseline, 49.9% (1223/2452) were female, 8.1% (199/2452) had low birthweight (<2500 g at birth), and 97.5% (2391/2452) of children had a child health card. On average, mothers were 28 years old and considered literate. Fathers were slightly older, with an average age of 31.5 years at baseline, and had slightly higher education levels than mothers. The average household consisted of 2.5 adults and 1 additional child (sibling).

**Table 4 table4:** Descriptive statistics.

Characteristics	Control (n=962)				Home visits (n=315)				Afini (n=1175)		
	Observations, n	Clusters, n	Mean (SE)	Observations, n		Clusters, n	Mean (SE)	Observations, n		Clusters, n	Mean (SE)
Child age (months)	959	67	5.0 (0.11)	315		19	5.1 (0.22)	1169		78	5.1 (0.10)
Child is female	954	67	0.51 (0.02)	314		19	0.48 (0.03)	1172		78	0.50 (0.01)
Child has a health card	959	67	0.98 (0.01)	315		19	0.97 (0.01)	1169		78	0.98 (0.01)
Child born <2500 g	949	67	0.08 (0.01)	308		19	0.10 (0.02)	1152		78	0.08 (0.01)
CREDI^a^ score	950	67	43.0 (0.066)	307		19	43.0 (0.163)	1163		78	43.2 (0.065)
Mother’s age (years)	945	67	27.7 (0.26)	311		19	28.6 (0.48)	1155		78	28.0 (0.22)
Mother is literate	941	67	0.98 (0.01)	307		19	0.97 (0.01)	1151		77	0.99 (0.004)
Mother education level	944	67	3.2 (0.08)	310		19	3.2 (0.23)	1154		78	3.4 (0.08)
Father’s age (years)	843	66	31.2 (0.26)	277		18	32.1 (0.52)	1027		76	31.6 (0.26)
Father is head of household	844	66	0.94 (0.01)	277		18	0.94 (0.02)	1026		76	0.94 (0.01)
Father education level	832	66	3.5 (0.07)	267		18	3.5 (0.22)	1007		76	3.7 (0.07)
SES^b^ index	957	67	2.9 (0.12)	315		19	3.1 (0.29)	1169		78	3.2 (0.12)
Stimulation index	868	66	3.4 (0.06)	285		19	3.4 (0.14)	1076		78	3.5 (0.06)

^a^CREDI: Caregiver Reported Early Development Instruments.

^b^SES: socioeconomic status.

We anticipate completing the endline assessments in September 2024 and presenting final trial results to the local and national governments in Peru in early 2025.

## Discussion

### Principal Findings

In this study, we present the design and setup of a cluster randomized trial to evaluate the effectiveness and cost-effectiveness of Afini, a digital platform that provides digital support to children from 0 to 7 years of age. The trial compares the developmental improvement achievable through the Afini platform to developmental improvements achievable through home visits, which currently are considered the gold standard in this field. While home visits offer the advantage of personal interactions with caregivers, the main benefits of new technologies, such as Afini, lie in their flexibility. Using a chatbot and AI system, Afini efficiently and automatically takes into account the caregiver’s and child’s preferences. It then offers age-specific recommendations for development-promoting activities that parents can undertake with their children whenever they have the time for such interactions. The platform also provides advice on early child development, well-being, and health similar to the contents typically delivered through ECD home visits.

The proposed trial is innovative and timely for several reasons. Due to the rapid global increase in cell phone coverage [25], there are now unprecedented opportunities for health and education systems to interact with patients and families and intervene at scale effectively and efficiently [31,33,34]. These advances have paved the way for the development and use of parenting support platforms as a means of engagement [26,30,43,45,46]. However, several key questions must be addressed before such platforms can be used in remote and resource-constrained settings. These include understanding their reach and actual impact on child development. Additionally, it remains unclear whether these technologies can be scaled to populations with limited digital literacy.

Understanding the extent to which digital platforms can reach low-income communities and families is crucial for understanding the feasibility and effectiveness of digital platforms in addressing the needs of vulnerable populations. During our formative research, we were particularly concerned about the challenges related to technology access, internet connectivity, and affordability. However, our early findings indicated that the large majority of mothers with young children had internet and smartphone access. Furthermore, 2 months after baseline, 84% of mothers reported using the platform at least once, and 87% rated it as useful [35]. Similar studies conducted in LMICs have also reported high acceptance of digital parenting interventions [47,48] and good reach for mobile health interventions to improve maternal and child health [31,34]. However, the majority of existing data on digital parenting support interventions during early childhood has been collected in high-income countries [27,30,33,43]. While those studies show promise in parenting outcomes and engagement, such as enhancing parental self-efficacy [49,50], data from LMIC contexts are largely missing. Furthermore, to date, limited data exist on digital parenting interventions’ impact on child development, with few randomized controlled trials [51], and many studies still in the piloting stages, with small samples, or in ongoing data collection [52-54].

Our second question revolves around the impact of digital platforms on caregiver-child interactions and child development in low-resource communities. Caregiver-child interactions are vital for a child’s early development, and it is important for a digital platform targeting households in low-resource communities to facilitate positive and developmentally appropriate caregiver-child interactions. A study conducted in the United States examined the availability and quality of the apps in app stores and found very few apps offering tailored materials to parents instead of promoting generic guidance that may have limited usefulness in certain contexts [55]. However, several pilot studies demonstrated that digital interventions are feasible, engaging, and cost-effective ways for delivering developmental education to families, particularly in enhancing language-promoting behaviors [56,57]. A recent review highlighted the potential of mobile health and apps to promote early language development as well, although it raised concerns about the frequency and consistency with which parents will access and use digital interventions in their daily lives [58].

From a policy perspective, scalability is maybe the most critical aspect to consider when evaluating a digital platform. It is important to assess whether the platform can be successfully extended to other settings and populations beyond the initial study in the rural Andes. This becomes especially relevant when there is a possibility of limiting access for subsets of the population with varying levels of digital literacy, particularly in the absence of guidelines or follow-up assistance. Initial data collected in the study area showed that smartphone access and connectivity are almost universal [35]. While there have been limited studies demonstrating scalability thus far, it is essential to identify any unanticipated limitations or challenges that may arise during implementation and adherence, particularly in populations with diverse levels of digital literacy.

The proposed study has some limitations. First, while all intervention content was carefully adapted and is thus optimized for the local context studied, the materials used (and results obtained) may not directly work and translate to other settings. Second, our study is only able to follow-up children for about 2.5 years and can thus only give short-term treatment effects that may not fully capture long-term gains for treated children. Third, our intervention focused primarily on a broad measure of child development and did not offer specific insights into more narrow areas of early childhood health such as nutrition or emotional development. Future studies will be needed to address these issues.

### Conclusions

This trial will provide valuable insights into the impact and scalability of tailored digital ECD platforms, particularly in reaching remote and vulnerable populations in low- to middle-income settings, and address challenges faced by home visiting models, such as cost and sustainability. We wish to demonstrate the platform’s effectiveness, especially among diverse population groups with varying levels of digital literacy. This is crucial for designing effective future interventions.

## Abbreviations

AI: artificial intelligence
ARI-CP 2-5: Attachment Relationship Inventory Caregiver Perception 2-5 years
ECD: early child development
GSED: Global Scales for Early Development
LMIC: low and middle-income countries
PNCM: Programa Nacional Cuna Más
